#### Analysis of secondary endpoints

To investigate the effect of the intervention on the secondary outcomes, mean differences with respective 95% CI will be reported. If normality is not observed for any of the continuous secondary outcomes, the same strategy adopted for the primary outcome (use of a non-parametric equivalent to the Student’s t-test) will be used.

#### Pre-specified subgroup analysis

No formal subgroup comparative analysis is planned for the primary or secondary outcomes. However, the effect of the intervention on the primary outcome within subgroups will be presented using forest plots to visually examine whether it may differ according to some variables such as: (i) journals that actively implement the CONSORT Statement (defined as requiring authors to submit a completed CONSORT checklist alongside their manuscript) versus journals that are not actively implementing the CONSORT statement, (ii) sample size of included RCTs (n<100 vs n≥100) and (iii) impact factor (<5, 5.1–10;>10) as there is evidence that higher impact factor and higher sample size are associated with higher adherence to reporting guidelines.^35^ Subgroup analysis at the journal level will only be conducted when sufficient journals are in each group so that no results of individual journals are revealed. All analyses will be exploratory, with the aim of supporting new hypothesis generation, rather than being conclusive.

### Data management and confidentiality

Outcomes from publications will be assessed and extracted in duplicate. Since this information is not confidential, we will use freely available online forms (eg, Google forms) for data extraction from published RCTs. Data entered will be validated for completeness.

Data from the journal’s editorial system (eg, title of manuscript, first author, randomisation ID, journal, date when manuscript was assigned to an editor, date when the final decision was made, final editorial decision, number of peer reviewers who reviewed the manuscript, the peer review reports (if available)) will be extracted (by BS or a member of the journal’s staff), anonymised and entered in password protected files which are saved on a server from the University of Oxford. Data will be managed and curated according to University of Oxford regulations, which includes regular back-up (on a daily basis) of the virtual drives where the data are stored. No auditing or data monitoring is planned (as outcomes are directly extracted from journal’s editorial system or in duplicate from published RCTs).

The raw data extracted from the included published manuscripts can be made openly accessible in an anonymised way (ie, giving the included RCT a number instead of identifying them). Derived/aggregated data, including anonymised information generated from the journal’s editorial system, will be stored and made available to the research community when the project ends (see also ‘Publication policy and access to data’). Where appropriate, the researcher who has access to the journal’s editorial system (BS) and anyone else who will see the identifiable data will sign a confidentially agreement with the participating journals, confirming that they will not share identifiable data with any other party. Publishers such as the British Medical Journal (BMJ) state in their Company Privacy Statement that reviews and manuscripts may be used for quality improvement purposes and that is the nature of this research. Furthermore, peer reviewers for all BMJ journals receive the following statement in their invitation letter ‘We are constantly trying to find ways of improving the peer review system and have an ongoing programme of research. If you do not wish your review entered into a study please let us know by emailing […] as soon as possible.’

### Trial registration

This trial was denied registration on ClinicalTrials.gov as the study is not a clinical study that assesses a health outcome in human subjects. Instead we registered the trial on the Open Science Framework (https://osf.io/c4hn8). The first manuscript was randomised in July 2019. We expect that recruitment will be finished in summer 2021.

### Patient and public involvement

Given the specific study topic, the steering committee agreed that patient or public involvement is not needed for this study.

## Discussion

RCTs are the current gold standard for evaluating any new intervention in evidence-based medicine. Unfortunately, not all RCTs are of high quality. In fact, there are several well-known shortcomings with respect to reporting.^3 15–20^ It is important to note that adhering to the CONSORT Statement does not mean that the study is of high quality. However, reporting all items from the CONSORT checklist will enable readers to adequately judge the quality of RCTs.

In this RCT we will test if a simple intervention in the form of asking peer reviewers to check whether selected CONSORT items are adequately addressed will increase the proportion of reporting completeness in the published RCTs in the participating journals. A multicentre parallel arm RCT with randomisation at the individual manuscript level was chosen instead of a cluster RCT because the risk of ‘contamination’ at journal level was judged as low as the intervention will be implemented by an external researcher (ie, BS) or a member of the journal staff (eg, personnel from editorial services). The likelihood of contamination due to peer reviewers being invited to assess several RCTs and therefore becoming exposed to both intervention arms was judged small and therefore we do not plan to adjust for clustering by journal. Originally we planned to implement the intervention within the original instruction to peer reviewer email which is sent out as soon as a peer reviewer accepts the invitation from the journal. However, as these emails are sent automatically by the journal’s editorial system we would have needed to modify the software from each journal to make sure that only half of the manuscripts administered the intervention. After our first discussion with journal editors and journal staff, we realised that this approach is not feasible and therefore decided to implement the intervention in the form of a separate email. We intended to conduct this RCT in a pragmatic way so that results ‘would also be relevant to […] people who decide whether to implement the intervention on the basis of its results’.^36^ Hence we chose to assess outcomes from published articles and not from manuscripts after the first round of revisions. Ideally, the full impact of the intervention would also be measured including all versions of randomised manuscripts in the final statistical analysis. However, due to confidentiality issues and limited resources we will not be able to evaluate manuscript versions prior to publication.

A selection of CONSORT items was chosen instead of the entire CONSORT checklist as we did not want to put too high a burden on peer reviewers, which could increase the risk that peer reviewers ignore our reminder.

Should the proposed intervention be successful in improving the reporting quality of published RCTs, as measured by the adherence to CONSORT, the intervention could be implemented at the journal level without requiring a large amount of additional resources. In addition, very similar interventions for other article types (eg, systematic reviews, trial protocols) and corresponding guidelines (eg, PRISMA [Preferred Reporting Items for Systematic Reviews and Meta-Analysis], SPIRIT) could be easily implemented too.

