### Study design

This study is a multicentre superiority RCT with submitted manuscripts as the unit of randomisation (figure 1; allocation ratio 1:1). This study protocol was written in adherence to the SPIRIT guidelines (online supplementary file).^32^

10.1136/bmjopen-2019-035114.supp2Supplementary data

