Two authors of this protocol, working for *PLOS ONE* (IP and AC), one of the participating journals, pointed out that 3 out of the 10 assessed items (ie, item ‘Registration’, ‘Protocol’ and ‘Funding’) should always be implemented in submissions to their journal given their policy requirements for clinical trials. Assuming that this journal will recruit a high proportion of manuscripts, and that also other journals might update their templates, we increased the sample size in a second scenario, in which all these three items would have an overall adherence of 90% in the control arm (table 3). This would entail an overall baseline adherence with the 10 C-short items of 71%. Based on a two sided t-test, a sample size of 166 (83 per treatment arm) will have a power of 80% to find a 15% relative increase (71% adherence in control group; 82% adherence in intervention group; SD=0.25; a type 1 error at 5%).

Since the final sample size will be based on the number of articles published, rather than on the number of manuscripts randomised, eligible manuscripts will be randomised until 83 articles are published in each arm (resulting in no less than 166 articles), to avoid loss of power due to potential imbalance between arms. Recruitment will be stopped as soon as both arms reach the sample size of 83. After recruitment has stopped we will wait 3 months so that manuscripts, which are still in production, can be published. Manuscripts which are published after the 3-month period will be excluded.

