### Randomisation and blinding

Manuscripts meeting the eligibility criteria and sent out for external peer review by the journals will be randomised into one of the two groups (allocation 1:1). The randomisation list will be created by the Study-Randomizer system^34^ using random block sizes between 2 and 8 and stratified by journal. As soon as the first peer reviewer accepts the invitation, the manuscript will be included and randomised to one of the two study arms. One of the investigators (BS) will log onto the Study-Randomizer system^34^ and enter the study identification number (ID; provided by the journal), the study title and the journal the study was submitted to. Subsequently, all additional peer reviewers accepting the invitation to review the same manuscript will receive the same group assignment as the first peer reviewer.

Authors will be blinded to the intervention. Editors will not be actively informed about the randomisation (possible exception listed under ‘Interventions’). To avoid potential bias, peer reviewers and manuscript authors will not be informed of the study hypothesis, design and intervention.

Outcomes will be assessed in duplicate (see ‘Assessment of outcomes’). At least one outcome assessor will be blinded. Due to restricted resources the investigator conducting the randomisation (BS) might be involved in the data extraction from published manuscripts.

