#### Analysis of primary endpoint

The effect of the intervention will be estimated as the mean difference in the proportion of C-short items adequately reported between the study arms. If the data on the primary outcome are normally distributed, groups will be compared using an unpaired Student’s t-test. If the data are not normally distributed, comparisons will be performed using a non-parametric equivalent test (ie, Wilcoxon-Mann-Whitney test).

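### Journal stratifies the randomisation but is left out of the primary analysis for a reason that does not bear on it; the test stays valid but loses some precision

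*Protocol article*

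**What the plan says.** - **Unit.** Study design describes a "multicentre superiority RCT with submitted manuscripts as the unit of randomisation", allocated 1:1.
- **Randomisation.** Under Randomisation and blinding, the list is made "using random block sizes between 2 and 8 and stratified by journal".
- **Primary test.** Under Analysis of primary endpoint, if the data look normal, "groups will be compared using an unpaired Student’s t-test"; otherwise a Wilcoxon-Mann-Whitney test is used. Neither has a journal term.
- **Decision on journal.** The Discussion argues: "The likelihood of contamination due to peer reviewers being invited to assess several RCTs", and so meeting both arms, "was judged small and therefore we do not plan to adjust for clustering by journal". This is a stated decision with a stated reason, not a detail left to an analysis plan.
- **Journal as a predictor.** Under Sample size, staff of one participating journal report that registration, protocol and funding "should always be implemented in submissions to their journal given their policy requirements for clinical trials". That journal is expected to supply a large share of the manuscripts, and the planned control-arm mean was raised from 56% to 71%. The subgroup section also cites impact factor as associated with adherence.

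**The concern.** Two separate questions have been joined. Contamination asks whether a control manuscript's reviewers may have learned from the intervention, which would pull the arms together. Adjustment for journal asks whether outcomes are more alike within a journal than between journals. Contamination could be zero and journals could still differ widely.

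When randomisation is balanced within journals, differences between journals largely cancel from the treatment difference. An unadjusted test still counts those differences as noise. Its standard error is then larger than the true sampling error, so the confidence interval is somewhat wide and the test somewhat conservative. A model with a journal term recovers that precision. At stake is efficiency: a slightly wider interval and a few points of power on the primary outcome, given up for a reason that does not support the choice.

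**Working it through.** **1. The plan's own sample sizes.** Inputs are from the Sample size section: two-sided 5%, SD 0.25.

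- Scenario 1: difference 0.14, 68 per arm. The exact t calculation gives power 90.0%, as stated.
- Scenario 2: difference 0.82 − 0.71 = 0.11, 83 per arm. The exact t calculation gives 80.5%, as stated. The normal approximation used below gives 80.9%.

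**2. How much variance might journal carry?** The documents give no between-journal variance, so this is an assumption, bracketed with the protocol's Table 3. Suppose policy journals report the three items 100% of the time and the others follow the scenario 1 rates (69%, 19%, 34%).

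- Gap between the two kinds of journal: (31 + 81 + 66)/1000 = 0.178.
- Between-journal variance is f(1 − f)d², where f is the share of articles from policy journals. Divide by 0.25² = 0.0625 to get the share of variance, ρ.
- f chosen to give the planned 90% on the three items: their mean elsewhere is 40.7%, so f = (90 − 40.7)/(100 − 40.7) = 0.83 and ρ = 0.83 × 0.17 × 0.178²/0.0625 ≈ 0.07.
- f = 0.3 or 0.7: ρ = 0.21 × 0.178²/0.0625 ≈ 0.11. f = 0.5: ρ ≈ 0.127.
- Cruder alternative, half the articles at 71% and half at 56%: ρ = 0.25 × 0.15²/0.0625 = 0.09.

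A range of about 7% to 12% is reasonable. Zero is possible.

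**3. Consequence if balance within journals is complete.** The unadjusted standard error is SE = 0.25 × √(2/83) = 0.0388. The true standard error is SE × √(1 − ρ).

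- Type I error of the unadjusted test: 2[1 − Φ(1.96/√(1 − ρ))].
- Unadjusted power: Φ[(0.11 − 1.96 SE)/(SE√(1 − ρ))].
- Adjusted power: Φ[0.11/(SE√(1 − ρ)) − 1.96].

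| ρ | Type I error, unadjusted | Power, unadjusted | Power, adjusted | Excess CI width, unadjusted |
|---|---|---|---|---|
| 0 | 5.0% | 80.9% | 80.9% | 0% |
| 0.07 | 4.2% | 81.8% | 83.6% | 3.7% |
| 0.09 | 4.0% | 82.0% | 84.4% | 4.8% |
| 0.12 | 3.7% | 82.4% | 85.6% | 6.6% |

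The comparison must be made along a row. Stratification also raises the power of the unadjusted test, so setting adjusted power against the planned 80% would overstate the loss.

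**4. Effect of analysing published articles only.** Simulations used seven journals, blocks within journal, 83 per arm and 3,000 runs per setting. The Monte Carlo standard error is about 0.4 points for type I error and 0.7 for power. Publication rates are assumptions. At ρ = 0.10:

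| Published | Journal sizes | Type I error, unadjusted / adjusted | Power, unadjusted / adjusted |
|---|---|---|---|
| All | equal | 3.7% / 4.3% | 83.1% / 85.5% |
| All | one with half | 4.0% / 4.6% | 83.1% / 84.1% |
| 40% | equal | 5.6% / 5.7% | 80.8% / 82.9% |
| 40% | one with half | 4.7% / 5.0% | 80.3% / 82.0% |

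As publication thins the blocks, the unadjusted type I error returns towards 5%. A power gain of about 1 to 2 points from adjustment remains in each setting.

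**The case against.** The strongest reply is that nothing is invalid. The unadjusted comparison does not inflate false positives, is not biased by leaving journal out of a stratified design, and reaches the planned 80% power, since the SD of 0.25 is treated as the total SD. All of this stands.

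It is also fair that the 56% and 71% figures are not results for two kinds of journal. The first is the control-group mean of an earlier study and the second an assumed overall mean. The share of articles from the large journal is unquantified, and other journals may update their templates, which would shrink the differences. The size therefore rests on assumption.

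Three stronger readings are tempting:

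- **That ignoring clustering inflates type I error, as in a cluster trial.** Manuscripts are randomised within journals, so the error runs the other way, and no design-effect inflation of the sample size is called for.
- **That the interval is clearly too wide.** This holds fully only while balance within journals survives. The Populations of analysis section restricts the main analysis to published articles, so some balance will be lost.
- **That the trial is underpowered.** The calculations do not show it.

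What the reply leaves standing is that the reason given does not support the choice, and that a recorded factor expected to predict the outcome is left unused.

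**Conclusion.** The point holds as a recommended improvement in efficiency, with a correction to the rationale. The design stratifies by journal, the plan expects journal to predict adherence, and the analysis omits journal on an argument about contamination that does not address the question.

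If journal carries about 7% to 12% of the planned variance, adjustment is worth roughly 2 to 3 points of power under full balance. The unadjusted test is then mildly conservative, and closer to nominal when many manuscripts go unpublished. These figures assume a true difference of 0.11, a total SD of 0.25 and 83 published articles per arm. If journals do not differ, there is no loss.

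**What to change.** - Make the primary analysis a linear model of the proportion of C-short items adequately reported on arm plus journal, with journal as a fixed effect and very small journals pooled by a rule set in advance. Report the adjusted mean difference with its 95% CI.
- Keep the unadjusted comparison as a sensitivity analysis.
- In the Discussion, delete the inference from low contamination to no adjustment for journal. The contamination argument can remain as the reason for randomising manuscripts rather than journals.

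The cost is a change of wording and a few degrees of freedom. Journal is already entered at randomisation, so no new data are needed, and the sample size need not rise. The change should be fixed before outcome data are seen, so that the choice of model cannot look selective. Adding the RCTs' sample size as a covariate is optional and not part of this point.

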### Ethics and dissemination

Ethical approval has been obtained from the Medical Sciences Interdivisional Research Ethics Committee of the University of Oxford (R62779/RE001). The original approved study protocol is available in online supplementary appendix 2. The WHO trial registration data set is available in online supplementary appendix 3.

The results from this study will be published in a peer-reviewed journal irrespective of the study results. Authorship of publications will be granted according to the criteria of the International Committee of Medical Journal Editors. We plan to make the anonymised data set, including the data from the published articles, available as a supplementary file of the main publication.
